### Sample size calculation and statistics

Planned enrollment was at least 1234 patients. Initially, the design projected that 2 years of accrual, plus 5 years of additional follow-up would be sufficient to observe the target of 374 disease-free survival events across the two treatment arms, with 85 % power to detect 7 % reduction in hazard with OFS plus tamoxifen versus tamoxifen alone. In 2010, because of a slower-than-expected enrollment rate, the steering committee extended the accrual period from 2 years to 4 years.

An intent-to-treatment analysis and per-protocol analysis will be performed. The disease-free survival rate will be evaluated using the Kaplan-Meier method. The log-rank test will be used to compare the treatment groups. Multivariate analyses will be performed using Cox’s proportional hazards model.

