### Study design

The first screening test to evaluate ovarian function was performed within 3 months of the final dose of chemotherapy. Premenopausal status at the first screening test was defined by serum follicular stimulating hormone (FSH) levels < 30 mIU/ml. At 6, 12, 18, and 24 months following the baseline assessment, ovarian function status is to be evaluated by menstruation status and serum FSH levels. Regaining premenopausal status is defined by FSH levels < 30mIU/ml or bleeding history within 6 months of each visit. Study visits will be every 6 months for 5 years and at least yearly thereafter, according to each institute’s routine practice. If the patient does not regain satisfy the definition of being premenopausal during the 24 months after enrollment, the patient will be categorized to the permanent menopause group (group A). At each visit, newly confirmed premenopausal patients will be randomly assigned in a 1:1 ratio to the OFS group (group C or group E) or the tamoxifen alone group (group B or group D). The OFS group is treated with 3.6 mg subcutaneous injection goserelin (Zoladex® [D-Ser(But)^6^ Azgly^10^ luteinizing-hormone-releasing hormone]; AstraZeneca) every 28 days for 2 years plus oral tamoxifen at a dose of 20 mg daily for 5 years. The tamoxifen only group is treated with oral tamoxifen at a dose of 20 mg daily for 5 years. Randomization is performed by means of an internet-based system and is stratified according to lymph node status (negative versus positive) and institutes (Fig. 1). Data are collected and stored in a digital case report form.

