### Trial progress

Recruitment was closed on March 2014. Between March 2009 and March 2014, 1485 patients were screened, and 1483 patients from 35 institutes in South Korea were enrolled in this study. On January 12 2015, 634 patients were randomized to the OFS group, and 655 patients were randomized to the tamoxifen only group (Table 2). Eighty patients were classified as permanent menopause status. Another 114 patients continue to exhibit a status of chemotherapy-induced amenorrhea, and the ovarian function of these patients is being evaluated every 6 months. All of the patients received chemotherapy before randomization. Node-positive disease was present in 56.3 % of the patients. The first interim analysis will be performed when 50 % of the planned disease-free survival events (187 events) have occurred.

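### 374 events cannot give 85 % power for a 7 % hazard reduction: power for that effect is about 10 % (17 % one-sided), and 374 events detect a reduction of about 24 to 27 %

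*Protocol article*

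**What the plan says.** The section on sample size calculation and statistics gives the whole quantitative basis of the design:

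- Size: "Planned enrollment was at least 1234 patients".
- Duration and events: 2 years of accrual plus 5 years of follow-up were projected to be "sufficient to observe the target of 374 disease-free survival events across the two treatment arms".
- Power and effect: the same sentence claims 85 % "power to detect 7 % reduction in hazard with OFS plus tamoxifen versus tamoxifen alone".
- Test: "The log-rank test will be used to compare the treatment groups".

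The Study design section says that "newly confirmed premenopausal patients will be randomly assigned in a 1:1 ratio". The Trial progress section repeats the event target indirectly: the first interim analysis is due when 50 % "of the planned disease-free survival events (187 events) have occurred", and 2 × 187 = 374. The end points section puts the primary comparison on the scale of 5-year DFS rates. The article states no alpha, sidedness, control-arm DFS rate or hazard ratio.

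**The concern.** A 7 % reduction in hazard is HR 0.93. Effects that small need thousands of events, so 374 events with 85 % power looks wrong on sight. The event count is not a misprint, because the interim figure of 187 confirms it.

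This is the only statement of the effect the primary comparison was sized for. If it stands, a reader is told that the trial can detect a very small effect when it was sized for a much larger one, and could misjudge what a non-significant result means. Anyone who took the design alternative from this sentence, for example to compute conditional power at the interim, would start from the wrong value.

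**Working it through.** **Inputs from the article.** Events d = 374; power 85 % (z = 1.036); effect HR 0.93; allocation 1:1; log-rank test; at least 1,234 patients planned; 2 + 5 years; 1,483 enrolled, of whom 634 + 655 = 1,289 had been randomised by January 2015.

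**Assumption.** Alpha is not stated. I take two-sided 5 % (z = 1.960) and also show one-sided 5 % (z = 1.645).

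**1. Trying to reproduce the 374.** Schoenfeld's formula for 1:1 allocation is d = 4(z_α + z_β)² / (ln HR)², with ln 0.93 = −0.0726.

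- Two-sided 5 %: 4 × (2.996)² / (0.0726)² ≈ 6,820 events (Freedman's formula: 6,826).
- One-sided 5 %: 4 × (2.681)² / (0.0726)² ≈ 5,461 events (Freedman: 5,466).

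The stated 374 is not reproduced. Both results exceed the number of women enrolled.

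**2. Power that 374 events give at HR 0.93.** Power = Φ(|ln HR| × √d / 2 − z_α), and 0.0726 × √374 / 2 = 0.702.

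- Two-sided 5 %: Φ(0.702 − 1.960) = 10.4 %.
- One-sided 5 %: Φ(0.702 − 1.645) = 17.3 %.
- One-sided 20 %: 44 %.

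For 85 % power the critical value would have to be 0.702 − 1.036 = −0.334, a one-sided alpha of about 0.63. No usable alpha rescues the statement. Even if all 1,289 randomised women had an event, power at two-sided 5 % would be only about 26 %.

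**3. What 374 events do detect at 85 % power.** HR = exp(−2(z_α + z_β) / √374).

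- Two-sided 5 %: exp(−0.310) = 0.734 (Freedman: 0.732), a reduction of about 27 %.
- One-sided 5 %: exp(−0.277) = 0.758, a reduction of about 24 %.

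**4. Is the 7 % an absolute difference in 5-year DFS?** The control rates below are assumptions. HR = ln(S₁) / ln(S₀). The two-proportion N uses the pooled-variance formula. Expected events assume exponential survival, 1,234 patients, uniform accrual over 2 years, 5 further years of follow-up and no dropout.

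| Assumed 5-year DFS | Alpha | HR | Events needed (Schoenfeld) | Two-proportion N | Expected events |
|---|---|---|---|---|---|
| 70 % vs 77 % | two-sided 5 % | 0.733 | 372 (Freedman 378) | about 1,425 | 380 |
| 75 % vs 82 % | two-sided 5 % | 0.690 | about 260 | 1,234 | about 311 |
| 66 % vs 73 % | one-sided 5 % | 0.757 | about 372 | about 1,242 | 436 |

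The first row fits the event target and the 2 + 5-year timetable approximately. The second fits the planned N exactly but not the event target. The third comes close to both 374 and 1,234, but only with a one-sided test. All three read the 7 % as percentage points, and they disagree on the control rate, the HR and the sidedness.

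**The case against.** The strongest case on the other side accepts the arithmetic and limits what follows from it.

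- **A reader might infer that HR 0.73 was the design alternative.** The text does not support this. HR 0.73 is what 374 events detect at an assumed two-sided 5 %. The 70 % vs 77 % pair was chosen to fit, matches 374 only approximately, and gives a two-proportion N of about 1,425. The candidates above run from HR 0.69 to 0.76. This objection stands.
- **A reader might infer that the interim or a futility calculation was run on HR 0.93.** Nothing shows this. The interim is triggered by an event count, and the article contains no futility rule or conditional-power calculation. The harm there is a risk to avoid, not an established error. This also stands.
- **A reader might infer that the event target is wrong or the trial too small.** That does not follow. 374 events is an ordinary target for a hazard reduction of 24 to 27 %, so the stated effect is the likelier error.
- **It is only an article, and the full protocol may have it right.** That may be so, but the fault is not a missing detail. The sentence gives an effect, a power and an event count that exclude one another, and nothing elsewhere in the article corrects it.

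**Conclusion.** The sentence is wrong as written. Power for a 7 % hazard reduction is about 10 % (two-sided 5 %) or 17 % (one-sided 5 %), against the 85 % claimed. The events needed are about 6,800 or 5,460, roughly 18 or 15 times the 374 planned. The conclusion rests on the article's own event count, power, effect, allocation and test. The alpha is assumed, but no usable alpha changes the result.

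That an absolute 7-point difference in 5-year DFS was reported as a relative hazard reduction is a likely explanation, since the primary end point is on that scale. It remains an inference: the control rate, HR, alpha and sidedness of the original calculation cannot be recovered from this text.

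**What to change.** Replace the wording on the 7 % hazard reduction with the effect the design supports. At 85 % power, 374 events detect HR about 0.73 at two-sided 5 %, or about 0.76 at one-sided 5 %. Which applies depends on the original calculation, so the sponsor should:

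1. take the two 5-year DFS rates, the HR, alpha and sidedness from that calculation and state them;
2. show how they lead to both 374 events and 1,234 patients, because the candidate readings do not all satisfy both;
3. base any interim or conditional-power work on that confirmed alternative and not on HR 0.93.

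The cost is one corrected sentence and a look at the original calculation. No more patients are needed to correct the wording, though the stated detectable effect becomes less favourable. If the original basis proves to be one that does not lead to 374 events, such as 75 % vs 82 %, the event target will also need an explanation.

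### Randomization is stratified by nodal status but the log-rank comparison is worded without strata; as worded, the test is valid but slightly conservative, and one sentence would settle it

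*Protocol article*

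**What the plan says.** Under Study design, the protocol article states that randomization "is stratified according to lymph node status (negative versus positive) and institutes", with 1:1 allocation. Under Sample size calculation and statistics, the treatment comparison is described in one sentence: "The log-rank test will be used to compare the treatment groups". The next sentence adds that "Multivariate analyses will be performed using Cox’s proportional hazards model", without listing covariates.

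The same section gives "the target of 374 disease-free survival events across the two treatment arms" as the basis for 85 % power. Trial progress reports 35 institutes, 56.3 % node-positive patients, and a first interim analysis at 187 events.

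**The concern.** Stratified randomization balances nodal status between the arms. If nodal status is prognostic, that balance removes part of the chance variation in the treatment comparison. A log-rank test that ignores the strata still includes that variation in its variance, so it rejects slightly less often than its nominal level. It also compares arms that each mix low-risk and high-risk women, which weakens the marginal effect relative to the effect within nodal groups.

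At stake is a small amount of power in a trial whose size is fixed by its event count. The trial already holds the information needed to recover it. A smaller matter is clarity: a reader of this section cannot tell which log-rank test will decide the primary comparison.

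**Working it through.** **Inputs from the article.** 374 events, planned N 1234, 85 % power, 1:1 allocation, 2 years of accrual as first planned (later 4), 35 institutes. Node-positive share from Table 2: (371 + 355) / (655 + 634) = 726 / 1289 = 56.3 %.

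**Inputs assumed.** Two-sided alpha 0.05, control 5-year disease-free survival 70 %, exponential survival, and a nodal hazard ratio (positive versus negative) of 1.5 to 4. The article gives none of these.

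**Step 1: the plan's own figure.** Schoenfeld's formula for 1:1 allocation is D = 4(z₀.₉₇₅ + z₀.₈₅)² / (ln HR)², with z₀.₉₇₅ + z₀.₈₅ = 1.960 + 1.036 = 2.996.
- Taken literally, the effect in "with 85 % power to detect 7 % reduction in hazard with OFS plus tamoxifen versus tamoxifen alone" is HR 0.93. Then D = 4 × 2.996² / (ln 0.93)² ≈ 6820, and 374 events give 10.4 % power. The stated figure does not reproduce.
- Read as 7 percentage points of 5-year disease-free survival, 70 % versus 77 %, HR = ln 0.77 / ln 0.70 = 0.733. Then D = 372, and 374 events give 85.2 % power. This reproduces.
- Solving for the HR at 374 events and 85 % power gives exp(−2 × 2.996 / √374) = 0.7335.

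The second reading is used below. The wording of the effect size is a separate matter.

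**Step 2: simulation.** N = 1234, analysis at the 374th event, 56.3 % node-positive, arms balanced within each nodal group, within-stratum HR 0.7335. The unstratified log-rank test is compared with the node-stratified one. The 1.5, 2, 3 and 4 rows come from 20,000 trials each (Monte Carlo error about 0.25 points on power and 0.15 on type I error). The 2.5 row comes from 4,000 trials (error about 0.6 points on power).

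| Assumed nodal HR | Power, unstratified | Power, stratified | Loss (points) | Two-sided type I error, unstratified |
|---|---|---|---|---|
| 1.5 | 84.4 % | 84.7 % | 0.3 | 4.9 % |
| 2 | 84.1 % | 85.0 % | 0.9 | 4.6 % |
| 2.5 | 84.3 % | 85.9 % | 1.6 | not run |
| 3 | 82.7 % | 84.8 % | 2.1 | 4.2 % |
| 4 | 81.7 % | 84.9 % | 3.2 | 4.0 % |

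Other runs of 4,000 and 8,000 trials gave losses of 0.1 to 0.7 points at nodal HR 1.5, 0.8 to 1.0 at 2, 1.7 to 2.5 at 3, and 3.0 to 3.8 at 4. In the 8,000-trial run, unstratified type I error was 4.8, 5.0, 4.1 and 3.9 % at nodal HR 1.5, 2, 3 and 4.

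**Step 3: the hazard ratio.** Mean estimate over 4,000 trials, Cox model without nodal status versus stratified by it: 0.738 versus 0.733 at nodal HR 2, and 0.7485 versus 0.7332 at nodal HR 4. The largest shift is 0.7485 − 0.7332 = 0.015.

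**Step 4: the loss in events.** Restoring 85 % power takes 374 × [(1.960 + z₀.₈₅) / (1.960 + z_p)]² − 374 further events, where p is the power of the unstratified test.
- From 84.1 % (z = 0.999): about 10 events.
- From 81.7 % (z = 0.904): about 35 events.

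**Step 5: institute as a stratum.** 35 institutes × 2 nodal groups = 70 cells, and 374 / 70 ≈ 5 events per cell. Strata that thin would themselves lose information.

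**The case against.** The strongest objection is that the article never says the test is unstratified. It condenses a fuller protocol, and whether a log-rank test is stratified is commonly settled there or in the SAP. Stratified randomization and the words used for the test do not contradict each other. This stands: a reader might infer that an unstratified test is the settled plan, but the article shows only that no strata are named.

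A reader might also infer that the reported hazard ratio will be attenuated. That is not established. A log-rank test yields no hazard ratio, and the only model named that does is a multivariate Cox model whose covariates are not listed; it may include nodal status. The shift in Step 3 applies only to an unadjusted estimate, and it is the difference between a marginal and a conditional effect rather than an error.

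Nor do the documents support saying that 85 % power is missed in general. At a nodal HR of 2 or below the loss is at most about one point, and even that depends on a nodal HR and an effect size that the article does not give.

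Finally, it may look inconsistent to ask for one randomization factor in the test and not the other. The event count per cell in Step 5 is a sound reason to leave institute out. Timing of randomization was not a randomization stratum and its effect has not been quantified here, so stratifying by it is optional and not part of this point.

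**Conclusion.** The point holds in a limited form. As worded, the comparison does not use a prognostic factor on which randomization was stratified. Such a test is valid and errs on the conservative side. The cost is about 0 to 1.5 points of power for a nodal HR of 1.5 to 2.5 and about 2 to 4 points for 3 to 4. Type I error is about 5 % at a nodal HR of 2 or below and about 4 % at 3 to 4.

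These sizes rest on the assumed nodal HR, on reading the 7 % as percentage points of 5-year disease-free survival, and on the assumed alpha and control rate. The direction depends only on nodal status being prognostic. This is a small improvement at almost no cost, not a flaw that threatens the trial's conclusion.

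**What to change.** Before the 187-event interim analysis, add to the analysis section that the primary log-rank test is stratified by lymph node status as randomized, and that the treatment hazard ratio comes from a Cox model stratified by, or adjusted for, nodal status. Add that institute is left out of the test strata because the cells would be too small.

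The words *as randomized* matter because Table 2 lists 5 + 4 = 9 randomized women with unidentified nodal status. Using the value entered at randomization gives one rule for them, provided the randomization system holds it.

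The cost is a sentence or two, with no new data and no change to sample size or conduct. If the full protocol or SAP already stratifies the test, no change is needed.

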Soonchunhyang University Colleage of Medicine
Soonchunhyang University College of Medicine, Bucheon Hospital
Sungkyunkwan University School of Medicine, Kangbuk Samsung Hospital
University of Ulsan, Asan Medical Center
Yeungnam University Hospital
Yonsei University College of Medicine

**Table 2 Tab2:** Demographics of randomized patients

	Tamoxifen only group (B + D group, *N* = 655)	Ovarian function suppression group (C + E group, *N* = 634)	*P*-value
Age(mean, years)	39.7 ± 4.1	39.6 ± 4.1	0.580
Stage			
I	178 (27.2 %)	169 (26.7 %)	0.977
II	335 (51.1 %)	332 (52.4 %)	
III	121 (18.5 %)	113 (17.8 %)	
Unidentified	21 (3.2 %)	20 (3.2 %)	
Lymph node status			
Negative	279 (42.6 %)	275 (43.4 %)	0.927
Positive	371 (56.6 %)	355 (56.0 %)	
Unidentified	5 (0.8 %)	4 (0.6 %)	
Histology			
Invasive ductal carcinoma	573 (87.5 %)	560 (88.3 %)	0.917
Invasive lobular carcinoma	32 (4.9 %)	26 (4.1 %)	
Others	42 (6.4 %)	41 (6.5 %)	
Unidentified	8 (1.2 %)	7 (1.1 %)	
Histologic grade			
G1	95(14.5 %)	118 (18.6 %)	0.229
G2	359 (54.8 %)	323 (50.9 %)	
G3	160 (24.4 %)	151 (23.8 %)	
Unidentified	41(6.3 %)	42 (6.6 %)	
Chemotherapy regimen			
Anthracycline + cyclophosphamide	184 (28.1 %)	185 (29.2 %)	0.782
Anthracycline + cyclophosphamide followed by taxane	324 (49.5 %)	318 (50.2 %)	
Anthracycline + taxane	30 (4.6 %)	29 (4.6 %)	
5-fluorouracil + anthracycline + cyclophosphamide	74 (11.3 %)	73(11.5 %)	
Others	21 (3.2 %)	14(2.2 %)	
Unidentified	22 (3.4 %)	15 (2.4 %)	
Operation			
Total mastectomy	268 (40.9 %)	248 (39.1 %)	0.762
Breast conserving surgery	382 (58.3 %)	382 (60.3 %)	
Unidentified	5 (0.8 %)	4 (0.6 %)	

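### The primary arm comparison states no covariates, although grade, stage, node status and age are on record; a prespecified adjusted analysis would be more efficient and would remove a small conditional shift towards OFS

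*Protocol article*

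**What the plan says.** All references are to the protocol article.

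- **Test.** Sample size calculation and statistics: "The log-rank test will be used to compare the treatment groups". No covariates or strata are stated for it.
- **Model.** The next sentence adds: "Multivariate analyses will be performed using Cox’s proportional hazards model". It names no covariates and does not say whether this model bears on the primary comparison.
- **Allocation.** Study design: randomization is 1:1 and "is stratified according to lymph node status (negative versus positive) and institutes".
- **Baseline data.** Table 2 reports age, stage, node status and "Histologic grade", among other factors, by randomized arm.
- **Numbers.** Trial progress: "634 patients were randomized to the OFS group, and 655 patients were randomized to the tamoxifen only group" as of 12 January 2015, with 114 women still under assessment. The first interim analysis comes at 187 of the 374 planned events.

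**The concern.** Grade, stage, node status and age are commonly treated as prognostic in early breast cancer, and the trial holds all four at baseline. On the plain reading, the test that decides the trial uses none of them. That matters in two ways.

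First, omitting strong prognostic factors from a time-to-event comparison pulls the marginal hazard ratio towards 1 and costs power, whatever the balance between arms.

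Second, grade was left to chance, and the allocation so far puts somewhat more G1 tumours in the OFS arm. Given that split, an unadjusted comparison credits a little of the better grade mix to OFS.

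The trial is open-label and the article fixes no covariates. Adjustment chosen after outcomes are visible would be open to challenge; adjustment fixed beforehand would not.

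**Working it through.** **1. Reproducing the article's figure.** Table 2, histologic grade:

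| | Tamoxifen alone (655) | OFS (634) |
|---|---|---|
| G1 | 95 (14.5 %) | 118 (18.6 %) |
| G2 | 359 (54.8 %) | 323 (50.9 %) |
| G3 | 160 (24.4 %) | 151 (23.8 %) |
| Unidentified | 41 (6.3 %) | 42 (6.6 %) |

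Pearson chi-square on all four rows is 4.32 on 3 df, P = 0.229, as printed. On the three graded rows P = 0.120. The collapsed contrast G1 versus G2/G3 among graded women (95/614 versus 118/592) gives P = 0.042, or 0.051 with continuity correction, but it was chosen after seeing the table.

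**2. Expected shift from grade mix alone, with no OFS effect.** The article gives no grade hazard ratios, so these are assumptions relative to G2, with unidentified set to 1. The formula is the grade-weighted mean hazard on OFS divided by that on tamoxifen alone. For G1 = 0.5 and G3 = 2:

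- tamoxifen alone: (95×0.5 + 359 + 160×2 + 41)/655 = 767.5/655 = 1.172
- OFS: (118×0.5 + 323 + 151×2 + 42)/634 = 726/634 = 1.145
- ratio: 0.977

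The standard error of the log hazard ratio at 374 events is 2/√374 = 0.103.

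| Assumed G1, G3 vs G2 | Ratio | Log ratio / SE |
|---|---|---|
| 0.8, 1.25 | 0.991 | −0.09 |
| 0.67, 1.5 | 0.985 | −0.15 |
| 0.5, 2 | 0.977 | −0.22 |
| 0.25, 3 | 0.969 | −0.31 |

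Simulations that add the stage counts (assumed stage I vs II of 0.6 / 0.5 / 0.4 and III vs II of 1.8 / 2.2 / 3.0, with G1 of 0.6 / 0.5 / 0.3 and G3 of 1.4 / 1.5 / 2.0) give a mean unadjusted hazard ratio of 0.98 / 0.97 / 0.96 under no effect. The overall range is about 1 to 4 %.

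**3. Error rates.** Over re-randomizations, with G1 = 0.5 and G3 = 2, the unadjusted log-rank test rejects in 5.0 % of runs, two-sided, so it is valid. Conditional on the Table 2 grade split, the two-sided rate stays at 5.05 %, but 4.0 % falls on the side of OFS against a nominal 2.5 %. A normal approximation agrees: Φ(−1.96 + 0.22) = 0.041. Across the assumed grade and stage effects, the conditional rate favouring OFS ran from about 3.5 to 5 %. Adjusting for or stratifying by grade and stage brought it to between 2.2 and 2.8 %.

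**4. Power.** Significance level and sidedness are not stated; two-sided 5 % is assumed. With 374 events and 85 % power, the detectable hazard ratio is exp(−(1.960 + 1.036) × 0.1034) = 0.7335. With that true effect and the assumed grade and stage effects:

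| | No covariates | Grade- and stage-stratified |
|---|---|---|
| Power over randomizations | about 76-82 % | 84-85 % |
| Chance of success given the Table 2 split | about 88 % | 84-87 % (adjusted or stratified) |

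A repeat of the power simulation gave 75 to 82 % and 85 %. The simulations draw grade and stage independently and do not model node status, which is linked to stage and already a stratum. The real gain from stage may therefore be smaller.

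**The case against.** The case against is substantial, and most of it stands.

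- **The log-rank test is valid.** A factor left out of the strata does not invalidate it. This stands; step 3 confirms it.
- **The imbalance is unremarkable.** Overall P is 0.229, G3 is level, and only one collapsed grade contrast falls near 0.05. Under pure chance, with factors treated as independent, at least one level-versus-rest contrast across the six categorical factors reaches P < 0.05 in about 51 % of trials. This stands. The imbalance is no reason to pick grade.
- **The article never says unadjusted.** It does not exclude a stratified log-rank test, and covariate lists are properly left to the full protocol or analysis plan. This stands: their absence from the article is no fault. What remains is that the article names a decisive test with no covariates and sets the Cox model apart.
- **Table 2 is a snapshot.** The 114 women still under assessment could change the split. This stands, and it limits the conditional figures but not the power argument.
- **Changing the primary analysis now is data-driven.** It would be, if grade were added because of Table 2. A list of recognised prognostic factors, including the balanced ones, fixed without sight of outcomes, is not. Given this split, it also lowers the chance of success for OFS.

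A reader might infer that part of any OFS benefit will be grade mix. The documents do not support that: they give no grade effect, the difference is compatible with chance, and the possible shift is at most about 0.3 standard errors from grade alone. Nor do two side issues bear on the trial's conclusion. The Table 2 P-values count unidentified as a level, but they are descriptive. Any loss of women with missing covariates would depend on a model that the article does not specify.

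**Conclusion.** The planned test is not wrong, and no bias over randomizations is shown. The point is one of efficiency and prespecification: a better primary analysis is available from data already collected. Under assumed prognostic effects, omitting grade and stage costs a few points of power, from about 2 when effects are mild to about 9 when they are strong. Given the split in Table 2, it may move the hazard ratio about 1 to 4 % towards OFS and raise false positives in that direction from 2.5 % to roughly 3.5-5 %, while the two-sided rate stays near 5 %. These sizes rest on assumed grade and stage hazard ratios, two-sided 5 %, 374 events and the January 2015 counts. The improvement is worth making, but it is modest.

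**What to change.** Before the 187-event interim and without reference to outcomes, state in the analysis plan:

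1. The primary treatment effect and test are the OFS hazard ratio from a Cox model adjusted for node status, stage (I/II/III), histologic grade (G1/G2/G3) and age. A log-rank test stratified on these factors is the alternative, but Cox is more practical: two node, four stage and four grade levels (counting unidentified) already make 32 cells, or about 12 events each at 374 events.
2. The factors are chosen because they are known to be prognostic, not because of Table 2.
3. The log-rank test is kept as a supporting analysis.
4. All randomized women stay in the model. Node status for the nine women listed as unidentified (5 + 4) is taken from the randomization record, since it was a stratum. Missing grade (41 + 42 = 83) and stage (21 + 20 = 41) are handled by an unidentified level or by imputation.

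The cost is analysis-plan wording and retrieval of nine values; no patients, visits or procedures are added. Two small downsides should be acknowledged: the hazard ratio becomes conditional on the covariates, and, given this split, the chance of success falls slightly, from about 88 % to 84-87 %.
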